### Sample size calculation

2.4

This study is an exploratory investigation, with the primary outcome measure defined as the reduction in the monthly migraine days (MMD) from baseline after 4 weeks of treatment. As a novel acupuncture technique, Fu’s Subcutaneous Needling (FSN) inevitably lacks high-quality randomized controlled trials (RCTs) to inform sample size estimation. Therefore, reference is made to an internationally rigorous RCT on acupuncture for migraine without aura (23), and the sample size is estimated based on this study, combined with clinical FSN practice and the current study design. The hypothesis posited comparable effect sizes between the two interventions (FSN group and flunarizine hydrochloride group) in this trial and those observed in the prior study’s acupuncture and flunarizine hydrochloride groups. The referenced study reported that after 4 weeks of treatment, the MMD in the acupuncture group decreased by 4.1 ± 3.5 from baseline, while the MMD in the flunarizine hydrochloride group decreased by 1.9 ± 2.3 from baseline. To verify whether the efficacy of FSN is at least not inferior to that of flunarizine hydrochloride, a non-inferiority test is employed. Based on previous research (24), the most commonly selected non-inferiority margin for Monthly Migraine Days (MMD) in migraine studies is 1. The calculation is performed using the Non-Inferiority Tests for the Difference Between Two Means in PASS 15.0 software. With *α* = 0.05 (two-sided), power (1−*β*) = 0.9, and an anticipated 25%dropout rate, a total of 44 participants (22 per group, 1:1 ratio) are required to detect a statistically significant difference in MMD changes between the two groups.

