### Secondary outcomes

4.2

Migraine-Specific Quality of Life (MSQOL) scores, including three dimensions: functional limitations (the degree to which migraines limit daily activities), dysfunction (the avoidance of certain activities due to the concern of migraine attacks), and emotional impact (the effect of migraines on mood), assessed via 14 items on a 6-point scale (0–5). Scores are calculated for each dimension.Headache diaries, recording daily migraine episodes, including presence/absence of headache, frequency, average duration, and use of acute analgesics (if taken, drug name, dosage, and frequency were documented). The reduction rate in rescue medication use was extracted as an independent outcome measure, calculated as the percentage decrease in monthly medication frequency and dosage from baseline to the end of treatment and throughout the follow-up period.Migraine Disability Assessment (MIDAS): This score evaluates migraine-related disability through five items (including the number of days that work, household chores, and social/leisure activities are affected by migraine; the score ranges from 0 to 270, with higher scores indicating greater disability).The difference in Visual Analog Scale (VAS) scores from baseline at week 4 of treatment.

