## Statistical analysis

6

Statistical analyses are conducted using SPSS 25. All tests employ two-sided comparisons, with statistical significance defined as *p* < 0.05.

Normally distributed continuous variables are presented as mean ± standard deviation (SD), whereas non-normally distributed variables are reported as median and inter-quartile range (IQR). Categorical variables appear as frequency and percentage (proportions).

For the MMD, MSQOL, MIDAS and VAS scale scores, between-group differences in changes from baseline to 4 weeks post-treatment are analyzed using either the independent *t*-test or Mann–Whitney U test, as appropriate. Intra-group comparisons between baseline and 4-week post-treatment measurements are conducted using paired *t*-test or Wilcoxon signed-rank test. Given the repeated measurements of MMD and the scale scores, repeated-measures analysis of variance (ANOVA) is additionally employed for supplementary analysis. For near-infrared spectroscopy (NIRS)-derived oxygen saturation levels, analyzed for within-group differences before and after treatment using paired *t*-test.

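### The between-group tests of change in MMD and the scale scores leave out the baseline value as a covariate; adding it gains precision from data already collected, by an amount that depends on an undocumented correlation

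*Protocol article*

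**What the plan says.** All places are in the protocol article.

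- **Between-group test (Statistical analysis).** For MMD, MSQOL, MIDAS and VAS, "between-group differences in changes from baseline to 4 weeks post-treatment are analyzed using either the independent" t-test or the Mann-Whitney U test. No covariate is named. The section also states: "All tests employ two-sided comparisons, with statistical significance defined as" p < 0.05.
- **Longitudinal analysis (same section).** Because the measures are repeated, "repeated-measures analysis of variance (ANOVA) is additionally employed for supplementary analysis".
- **Schedule (Study setting; Table 1; Follow-up and recurrence assessment).** MMD and the scales are taken at baseline, at Day 28 and at six post-treatment visits. Day 28 is the first MMD value after baseline, and the Primary outcome section makes it the primary time point.
- **Sample size calculation.** Inputs are "the MMD in the acupuncture group decreased by 4.1 ± 3.5 from baseline" and "the MMD in the flunarizine hydrochloride group decreased by 1.9 ± 2.3 from baseline", a non-inferiority margin of 1 day, alpha of "0.05 (two-sided), power" of "0.9, and an anticipated 25%dropout rate", giving 44 participants, 22 per group.
- **Rescue use (Secondary outcomes).** The reduction rate is "calculated as the percentage decrease in monthly medication frequency and dosage from baseline to the end of treatment" and through follow-up.

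**The concern.** A change score takes the baseline off with a fixed coefficient of 1. ANCOVA estimates the coefficient from the data, so its residual variance is never larger. In a trial of 22 per arm with 25% expected dropout, unused precision matters. It is available here without another patient or visit, because baseline MMD is already collected.

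Two related choices in the same analysis are also weak:

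- Repeated-measures ANOVA in its conventional form needs a complete row for every patient, yet the plan has seven post-baseline assessments and expects a quarter of patients to drop out.
- A percentage decrease in rescue use cannot be computed for a patient with no baseline use, and the inclusion criteria do not require any.

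These methods are stated in the text, so the point does not rest on something left to an analysis plan that is not shown.

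**Working it through.** **1. Reproduce the plan's figure.** From the Sample size calculation: assumed difference 4.1 − 1.9 = 2.2 days in favour of FSN; margin 1; distance to the margin 2.2 + 1 = 3.2; SDs of change 3.5 and 2.3. By noncentral t at 90% power:

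- one-sided 0.05: 16 per arm; 16/0.75 = 21.3, so 22; total 44, as stated;
- two-sided 0.05 (one-sided 0.025): 20 per arm; 20/0.75 = 26.7, so 27; total 54.

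The stated 44 therefore follows only if 0.05 is one-sided.

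**2. Power of the planned change-score t-test, 16 completers per arm.** SE = √(3.5²/16 + 2.3²/16) = √(17.54/16) = 1.047. Noncentrality = 3.2/1.047 = 3.06 on 30 df. Power is 84.1% at two-sided 0.05 and 91.0% at one-sided 0.05.

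**3. Effect of baseline adjustment.** Let s be the common SD at baseline and Day 28, and r their correlation.

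- Var(change) = 2s²(1 − r)
- Var(ANCOVA) = s²(1 − r²)
- Ratio = (1 + r)/2

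The SE in step 2 is multiplied by √[(1 + r)/2], with the same ratio assumed in both arms. The article gives no r, so a range is shown (two-sided 0.05, 16 per arm):

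| Assumed r | Variance ratio | SE | Power | Total N for 90% |
|---|---|---|---|---|
| Unadjusted | 1 | 1.047 | 84.1% | 54 |
| 0.3 | 0.65 | 0.844 | 95.6% | 36 |
| 0.5 | 0.75 | 0.907 | 92.7% | 40 |
| 0.6 | 0.80 | 0.936 | 91.1% | 44 |
| 0.7 | 0.85 | 0.965 | 89.4% | 46 |
| 0.8 | 0.90 | 0.993 | 87.6% | 48 |

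The degree of freedom spent on the covariate changes these powers by about 0.1 point.

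**4. If the SDs differ.** With k = SD at Day 28 / SD at baseline, the ratio is k²(1 − r²)/(1 + k² − 2rk). At r = 0.5 it is 0.52 for k = 0.75 and 0.89 for k = 1.25. It never exceeds 1, because the denominator minus the numerator is (1 − rk)². The direction of the gain is therefore certain and its size is not.

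**5. Does a mixed model add to the primary result?** In a simulation with 22 per arm, 25% dropout all before Day 28, compound symmetry, known covariance and 1,000 runs, power for t-test / ANCOVA / baseline-adjusted mixed model was:

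- r = 0.3: 0.857 / 0.952 / 0.957
- r = 0.5: 0.858 / 0.930 / 0.933
- r = 0.7: 0.839 / 0.874 / 0.895

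Monte Carlo error is about 1 point. Nearly all the gain comes from the covariate. A patient lost before Day 28 has no post-baseline MMD for the mixed model to use.

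**6. Complete cases in the supplementary ANOVA.** 44 × 0.75 = 33 patients at the stated dropout.

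**7. If the treatments are truly equal.** The distance to the margin falls to 1. Power is 15.0% unadjusted, and 20.8%, 18.6% and 16.9% adjusted at r = 0.3, 0.5 and 0.7.

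**The case against.** The strongest reply is that nothing here is invalid. The endpoint is itself a change from baseline, randomisation makes the comparison unbiased, and the trial was sized on SDs of change, so test and sample size agree. That stands: the point concerns precision, not bias. Several stronger readings are tempting, and the article does not support them.

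- **That the plan ignores baseline.** It does not. A change score subtracts baseline, though not with the most efficient weight.
- **That adjustment recovers power lost through the choice of test.** The fall from about 91% to 84% comes from reading alpha as two-sided, not from using change scores. At r of 0.7 or above, adjustment does not bring power back to 90%.
- **That baseline MMD is a recalled count because it is taken on Day 0.** Table 1 lists headache diaries at baseline, and the recurrence definition refers to diary records. The article does not say how the preceding month was counted.
- **That the plan drops incomplete patients.** The text does not say so. It is a property of conventional repeated-measures ANOVA, it affects an analysis labelled supplementary, and the handling of missing data may be set out elsewhere. Completer counts built on per-visit missingness would be pure assumption; the article supports only 25% overall.
- **That the within-arm paired tests mislead.** They accompany the between-group test, and the article does not rest comparative efficacy on them. Relabelling them would change no result.

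On rescue use, the article does not say whether the percentage is taken per patient or per group, and the Discussion separately promises a between-group comparison of medication use. The zero-baseline problem holds for the per-patient reading.

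**Conclusion.** The point holds as a worthwhile improvement in precision. The unadjusted change-score test is valid but less efficient than an analysis adjusted for a baseline already in hand. With 16 completers per arm, two-sided 0.05 and the plan's assumed 2.2-day advantage, non-inferiority power goes from 84% to 96% at r = 0.3 and to 88% at r = 0.8. Those figures rest on an undocumented r and on equal baseline and Day 28 SDs; unequal SDs could make the gain larger or smaller.

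The mixed model is worth having for the follow-up visits and hardly alters the Day 28 result. Baseline adjustment does not resolve the mismatch between the two-sided label and the one-sided alpha behind 44. Nor does it remove the reliance on an assumed advantage for FSN: under true equality, power stays at roughly 15% to 21%.

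**What to change.** In the Statistical analysis section:

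1. Make the primary analysis an ANCOVA of Day 28 MMD on arm and baseline MMD. Report the two-sided 95% confidence interval for the arm difference and compare it with the margin of 1 day, which that section does not currently apply. Name Day 28 explicitly, since the present wording could be read as four weeks after treatment ended. Treat MSQOL, MIDAS and VAS the same way, each with its own baseline; the margin applies to MMD only.
2. Replace the supplementary repeated-measures ANOVA with a mixed model for repeated measures containing arm, visit, arm-by-visit and the baseline value. The procedure is available in SPSS, the software already named.
3. Analyse rescue use as analgesic days per 28 days, taken from the headache diaries, in a count model adjusted for baseline use, in place of the percentage decrease.

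The cost is wording: same patients, visits, data and software. The change should be fixed before outcome data are examined. The alpha labelling and the assumed 2.2-day difference need their own correction.

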## Discussion

7

This study evaluate the efficacy of FSN versus flunarizine hydrochloride in improving pain, reducing headache frequency, and enhancing quality of life in patients with MWoA, while also comparing the adverse event profiles of both interventions. Additionally, the potential mechanisms underlying FSN therapy for migraine without aura are explored.

The treatment of migraine primarily involves preventive and acute-phase therapies. Preventive therapy can decrease the frequency, duration, and severity of migraine attacks, enhance patients’ quality of life, mitigate psychological comorbidities associated with frequent or chronic headaches, decrease reliance on such therapies, and prevent medication-overuse headaches (9). Based on clinical observations, empirical evidence, and supporting literature, commonly used and effective preventive medications for migraine include calcium channel blockers (e.g., flunarizine hydrochloride), antihypertensives (e.g., β-blockers), antiepileptics (e.g., topiramate, carbamazepine), and antidepressants (e.g., amitriptyline, fluoxetine) (1). However, most of these drugs are not specifically developed for migraine and exhibit tolerability and safety concerns, leading to poor patient adherence and challenges in migraine prevention.

Thus, identifying effective preventive treatments with minimal adverse effects is increasingly important. Emerging evidence highlights the role of muscular dysfunction in migraine without aura (9, 10, 32). As a novel acupuncture technique, FSN offers unique advantages. In FSN theory, “affected muscles” are defined as muscles or muscle segments exhibiting pathological functional changes (e.g., abnormal tension despite normal motor control) (33), analogous to myofascial trigger points (MTrPs) (34). Unlike trigger point therapy, FSN addresses functionally impaired muscles or abnormal muscle regions identified via palpation—rather than discrete “points”—through sweeping and reperfusion techniques. This approach significantly expands and accelerates muscle relaxation, improves local blood flow (35), and rapidly relieves functional pathological changes caused by ischemic muscle tension. In previous studies on trigger point therapy for migraine without aura, the sternocleidomastoid, trapezius, and splenius cervicis muscles are commonly selected as target muscles. During ischemic compression of trigger points in these muscles, sympathetic nerve activity in the trigger point region is suppressed, leading to reactive hyperemia (36). This process increases peripheral blood flow and facilitates the clearance of harmful substances within the muscle tissue (37), thereby alleviating pain—a mechanism that aligns with the reperfusion principle of FSN. Consequently, we hypothesize that FSN may be effective in migraine treatment.

The strengths of our study design include: (1) a rigorous comparative evaluation of FSN against the standard preventive drug flunarizine hydrochloride to assess its efficacy in migraine without aura, providing evidence for complementary and alternative therapies; and (2) the first application of near-infrared spectroscopy (NIRS) to measure cerebral cortical hemodynamic parameters, exploring FSN’s mechanism of action from a microcirculatory perspective, which may offer insights for further research and clinical application.

This study has several limitations. This study is a single-center trial with a small sample size (*n* = 60), which may be subject to selection bias, thereby limiting the generalizability of its findings to different populations or settings. Due to the inherent characteristics of acupuncture and pharmacotherapy, blinding both practitioners and participants presents considerable challenges, potentially increasing the risk of bias. To mitigate this risk, the intervention operators, outcome assessors, data collectors, and statisticians are all independent researchers. All personnel, except the operators, remained blind to group allocation. Standardized operating procedures are implemented to ensure adherence to treatment and assessment protocols, thereby minimizing unintended influences on outcome measures. The use of rescue medications may interfere with the evaluation of headache intensity and frequency; therefore, the final analysis will comprehensively document and compare intergroup medication usage (dosage, frequency, time to onset). Subsequent studies should establish unified guidelines. Limited by current equipment, near-infrared spectroscopy monitoring focused solely on hemodynamic changes in the prefrontal cortex and did not assess the effects of FSN on other brain regions. As an exploratory study, this trial aimed to investigate whether FSN may reduce patients’ reliance on flunarizine, decrease drug-related side effects, and provide a safe alternative for patients with contraindications to medication. Future large-scale, multi-center clinical trials are warranted to validate the long-term efficacy of FSN and its potential as an adjuvant or first-line treatment.

## Conclusion

8

The hypothesis of this study is that FSN therapy is not inferior to flunarizine hydrochloride in improving headache intensity and attack frequency in patients with migraine without aura, and that its therapeutic effects may be sustained over time. The study aims to test this hypothesis in a controlled clinical trial. The results may demonstrate the clinical utility of FSN therapy for migraine without aura and facilitate its wider implementation.
